**Varenicline as Treatment for Cognitive Deficits and Cigarette Smoking in Schizophrenia – Efficacy and Predictors**

**I BRIEF BACKGROUND AND RATIONALE-SUMMARY**

Most schizophrenic patients smoke cigarettes and many are heavy smokers and are very reluctant to stop smoking. There is some experimental evidence that administering nicotine to schizophrenic patients may improve some aspects of their cognitive function. There is also literature establishing abnormalities or deficits of the α7 nicotinic receptors associated in a complex way to schizophrenia. Varenicline is an α7 nicotinic agonist and we would predict that varenicline should benefit schizophrenia by improving cognitive function. It may have some of the cognitive benefits of nicotone administration and at the same time reduce cigarette smoking. If varenicline showed cognitive enhancement properties in patients with cognitive deficits in schizophrenia, this would be an important breakthrough in improving the longer term functional outcome of many patients with this illness. This provides a strong reason for conducting a careful study to evaluate whether adding varenicline to the medication of patients who are treated with standard antipsychotic medication will significantly improve their cognitive function. We also wish to tie in any beneficial effect of this drug to the abnormalities in reelin, GAD67, and DMNT1 mRNA in schizophrenia presented in the work of Costa, Guidotti, and Davis and their collaborators.

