**II RESEARCH PLAN**

***2.1 General Overview.***

This will be an 8 week parallel group placebo controlled double-blind experimental design in which cognitive function and psychopathology will be evaluated in schizophrenics (DSM IV diagnoses of schizophrenia or schizoaffective disorder). (Extension to 12 weeks at some sites including NKI site for smoking and psychopathology measures.) Patients will be tested on the MATRICS cognitive battery. Psychiatric status will be evaluated with the PANSS scale. Depression and any emerging suicidal ideation will be assessed by the CALGARY Depression scale. Negative symptoms for alogia and anhedonia will be assessed at beginning and end by abbreviated sections of the SANS scale. Changes in methylating enzyme functions related to GABAergic function will be assessed by measuring DNMT1 and GAD67 mRNAs in lymphocytes. These measures will be correlated with cognitive changes produced by varenicline. Because many schizophrenic patients are chronic cigarette smokers, and varenicline also affects cigarette smoking, cigarette smoking will be monitored by smoking questionnaires and nicotine and cotinine in plasma.

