***2.12 Cigarette Smoking Assessments***

Since smoking is highly prevalent in schizophrenic patients, varenicline has been shown to have antismoking effects in normals and in our preliminary studies also in schizophrenic patients], and it is also possible that nicotine itself has some cognitive effects, we will assess the degree of cigarette smoking in our subjects. Some e Measures will be taken at baseline and last month of study, and others at baseline 4, 8 weeks, and last month of study.

***A). Cigarette Dependence***. To measure at baseline the degree of dependence in current cigarette smokers, we will use the *Cigarette Dependence Scale* (Ettner et al 2003), in an interviewer-administered version.

***B).*** ***Self-report interview assessment***. Self-report of number of cigarettes smoked per day over the last week. Measurements will be made at baseline, 4 weeks, and end of study

***C) Smoking Urges***- A short version Tiffany Smoking urges scale (Cox, Tiffany, Chirsten 2001)

***D)*** ***Nicotine and Cotinine in plasma***. Measurements of plasma nicotine and cotinine will be made in plasma using samples at baseline, week 4 and week 8. It with be analyzed in the Analytical Psychopharmacology Laboratory ([name], director).

*Nicotine and Cotinine Assay*

Nicotine and cotinine are assayed in plasma in the Analytical Chemistry Laboratory at the Nathan Kline Institute for Psychiatric Research, director [name]. The assay is a GC/MS assay, following the procedure described in Davis (Davis1986) with modifications for GC/MS detection. The method involves liquid/liquid extraction with N - ethyl nornicotine and Nicotine D4 and Cotinine D3 as internal standards. Separation is achieved via gas chromatography with a Restek RtX-5 amine 15m 0.25ID 0.50 um df, crossbond 5% diphenyl 95% dimethylpolysiloxane column. Nicotine is run in PCI mode; target ion 163, cotinine is run in EI mode, target ion 98. The detection limit of accurate quantification of nicotine with this assay is 3 ng/ml with intra- and inter-coefficients of variation of 4.7 and 5.9%. Cotinine limit of detection is 5 ng/ml with intra- and inter-assay coefficient of variation of 3.4% and 5.2%.

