**III STATISTICAL ANALYSIS**

***3.1 General***

The primary dependent outcome variable, will be the average score on all tests of MATRICs battery (converted to T scores from different tests). Secondary cognitive analysis will be the of the hypothesized effects of attention-vigilance, verbal memory, and visual spatial memory. Secondary outcome variables will be cigarette smoking variables( cigarettes smoked, CO, nicotine and cotinine in plasma, smoking scores, Calgary depression scores).The general analysis approach will use a repeated measures analysis of variance. If there are appreciable missing data on measures with several ( >2) sequential testings a mixed model analysis will be used. If the data deviates significantly from normality, a non-parametric approach may be utilized using Wilcoxon matched pair’s signed-ranks, or Friedman’s two way analysis of variance. To examine whether there are differences in effects in patients with different degrees of cigarette smoking, we will compare smoking measures in patients assigned to placebo or active drug, and correlate effects on neuropsychological test changes with the smoking measures described above. Paired T-tests, or repeated measures ANOVA, will be used to analyze differences in the biochemical measures. Pearson or Spearman correlations will be used to examine the relationship between baseline neurochemical measures to cognitive tests performed at baseline, and both baseline neurochemical measure and change in these measures will be correlated with change in neuropsychological test scores. Additional analyses may use these neurochemical measures or changes during treatment as a covariate in an overall repeated measures analysis of variance.

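### Protocol 3.1 asks whether drug effects differ by smoking, and the title promises predictors, but the methods named do not test whether varenicline minus placebo varies with a baseline measure

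*Protocol*

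**What the plan says.** The title includes "Efficacy and Predictors", and Protocol 2.1 describes an "8 week parallel group placebo controlled double-blind experimental design", so a drug-minus-placebo contrast can be estimated at each level of a baseline measure.

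- **Smoking question (3.1):** "To examine whether there are differences in effects in patients with different degrees of cigarette smoking".
- **Smoking method (same sentence of 3.1):** "we will compare smoking measures in patients assigned to placebo or active drug, and correlate effects on neuropsychological test changes with the smoking measures".
- **Neurochemistry:** 2.1 says of the mRNA measures, "These measures will be correlated with cognitive changes produced by varenicline". In 3.1 the tool is a Pearson or Spearman correlation, applied both to the baseline value and to its change. Treatment arm is not mentioned.
- **Covariates (3.1):** "Additional analyses may use these neurochemical measures or changes during treatment as a covariate in an overall repeated measures analysis of variance".
- **Timing of smoking measures (2.12, Cigarette Smoking Assessments):** "Measurements of plasma nicotine and cotinine will be made in plasma using samples at baseline, week 4 and week 8". Section 3.1 does not say which time points enter the correlations. Section 2.12 also states that "varenicline has been shown to have antismoking effects in normals and in our preliminary studies also in schizophrenic patients".

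No treatment-by-baseline term, and no formal comparison of correlations between arms, appears anywhere.

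**The concern.** Whether effects differ by degree of smoking is a question about effect modification: does the difference between varenicline and placebo change with baseline smoking? Comparing smoking between arms answers another question, namely whether the drug reduces smoking. Correlating smoking or mRNA with cognitive change shows who changes, under either treatment. It cannot separate change caused by varenicline from prognosis or from practice effects, which 2.6 acknowledges for the mazes test.

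Two errors of interpretation follow. A marker that forecasts change equally in both arms can look like a predictor of varenicline response. A real modifier whose slopes run in opposite directions in the two arms can go unseen if the arms are pooled.

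The covariate sentence is a separate matter. Section I of the protocol wants to link any drug benefit to mRNA abnormalities, so on-treatment mRNA change is a proposed pathway. A treatment term adjusted for it answers a different question from the total drug effect.

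**Working it through.** **1. The plan's own figure.** Protocol 3.2 gives 15 or 29 per group for 80% power at α = 0.05 and an 18–28% improvement. It concerns the main effect only; nothing is given for predictors. No SD is stated, so it cannot be strictly reproduced. A two-sided two-sample t-test (sidedness assumed) has 80% power at d = 1.06 with 15 per group and d = 0.75 with 29. These imply SDs of 28/1.06 = 26.4 and 18/0.749 = 24.0 percentage points. A single SD of 24.0 gives 13 and 29 per group, close to the stated pair. I use d = 0.75 and 1.06 below as the size of the planned main effect.

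**2. Prognostic marker, no effect modification.** Inputs: 60 patients (3.2) less 10% dropout (the lower end in 2.2) is 54, or 27 per arm; within-arm correlation r = 0.4 between baseline marker and cognitive change, the same in both arms (assumed).

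Fisher-z power = Φ(atanh(r)·√(n−3) − 1.96), with atanh(0.4) = 0.424:
- pooled, n = 54: Φ(0.424 × 7.14 − 1.96) = Φ(1.07) ≈ 0.86
- active arm only, n = 27: Φ(0.424 × 4.90 − 1.96) = Φ(0.12) ≈ 0.55

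Simulation agrees:

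| Analysis | Share of trials with p < 0.05 |
|---|---|
| Correlation, arms pooled | about 86% |
| Correlation, active arm only | about 56% |
| Treatment-by-marker interaction | about 5% |

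The pooled 86% assumes no mean difference between arms. With a drug effect of 0.75 SD the pooled correlation falls to 0.4/√(1 + 0.75²/4) = 0.37 and Fisher-z power to about 0.80. The conclusion does not change.

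**3. The reverse case.** N = 60, slopes of −0.25 on placebo and +0.25 on drug (assumed). The pooled correlation is significant in 5% of trials, the active-arm correlation in 26% and the interaction in 45%.

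**4. Change correlated with change.** N = 60; the drug shifts the marker by 0.8 SD and cognition by 0.75 SD, with no link within arms (assumed). A pooled correlation is significant in 18% of trials instead of 5%.

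**5. On-treatment change as covariate.** Assumed values in model units (residual SD 1 in the first case, outcome SD 1 in the second); total drug effect 0.75; the drug shifts the marker by 0.8.
- Marker is a mediator with slope 0.4: adjusted effect = 0.75 − 0.8 × 0.4 = 0.43.
- Marker has no effect on cognition but shares a cause with it (loading 0.6 on each, so within-arm slope 0.6 × 0.6 = 0.36): adjusted effect = 0.75 − 0.8 × 0.36 = 0.46.
- Drug does not move the marker: the estimate stays at 0.75.

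**6. Power of the interaction test.** Binary modifier split 50/50, two-sided 0.05, SE = SD·√(16/N) = 0.516 SD at N = 60.
- interaction of 0.75 SD: Φ(0.749/0.516 − 1.96) = Φ(−0.51) ≈ 31%
- interaction of 1.06 SD: Φ(1.06/0.516 − 1.96) = Φ(0.09) ≈ 54%
- 80% power needs (1.96 + 0.84) × 0.516 = 1.45 SD

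At the enrolment cap of 100 (2.2) the two powers are about 47% and 76%.

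**The case against.** The other side has several fair points.

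- **Timing.** A reader might infer that all the predictors are measured after randomisation. The text does not support that: 3.1 names the baseline neurochemical measure, and 2.12 gives baseline smoking values. For these the fault is the missing interaction, not the timing.
- **Bias in the efficacy result.** A reader might infer that the drug comparison itself is compromised. It is not. On-treatment covariates appear only among optional additional analyses, and the primary comparison carries no such covariate.
- **Pooling.** Section 3.1 does not say that the correlations pool the arms, and the wording of 2.1 could mean the active arm alone. That lowers the false-lead rate from 86% to 56%. It does not rescue the method, since a single-arm correlation still cannot separate prognosis from drug response, and no formal comparison of arms is planned.
- **Purpose.** The neurochemical analyses are partly about mechanism, and smoking is a listed secondary outcome, so both the change-on-change correlations and the between-arm smoking comparison have legitimate uses. This stands; for neurochemical change the remedy is largely correct labelling.
- **Detail left to an analysis plan.** Model terms for exploratory analyses often are. Here, though, the protocol names a question and a method in one sentence, and the method does not answer the question.
- **Small gain.** The interaction test is weak at this sample size. That is true, but it calls for an exploratory label and an interval, not for testing something else.

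**Conclusion.** The point holds in this form. The mismatch between the smoking question and its method is fixed in the text of 3.1 and needs no assumption. The same gap affects the neurochemical correlations in so far as they are meant to deliver the predictors in the title.

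The sizes rest on assumed values: 86% pooled or 56% active-arm against about 5% requires a marker correlated 0.4 with change in both arms and 54 analysed patients. The covariate figures are illustrations only. The drop depends on how far the drug moves the marker and how the marker relates to cognition, and it is zero if the drug does not move it. What holds generally is that an estimate adjusted for a drug-affected marker cannot be read as the total drug effect.

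This bears on a titled aim and on secondary interpretation, not on the primary test, so it should be corrected but does not threaten the main result.

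**What to change.** Change section 3.1 as follows.

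1. For the smoking question and the predictors, fit a model of cognitive change with treatment, the baseline measure (baseline smoking or cotinine; baseline mRNA) and their product. Report the interaction estimate with its 95% CI, labelled exploratory.
2. Report correlations of smoking and neurochemical measures with cognitive change separately by arm, as description. Keep the between-arm comparison of smoking as what it is: a secondary outcome.
3. Allow only baseline values as covariates when estimating the drug effect. Report on-treatment changes only in exploratory mechanism (mediation) analyses.

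The cost is a few sentences and no new data, because the baseline measures are already scheduled. The downside is low power for the interaction tests, which should be stated with the results so that a non-significant term is not read as evidence of a uniform effect.

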***3.2 Power Analysis.***

It is difficult to do a power analysis using the MATRICS battery total score or sub-scores as outcome measures in the two groups (active vs placebo) because we have not utilized this battery in the past, and there is not substantial published data on changes with this cognitive measure in schizophrenic patients with a drug design similar to our own. We used N Query Advisor 3.0 to calculate hypothetical N’s required on various assumptions. Using an α=.05, and a two group univariate analysis of variance model, with a 18-28% improvement in group scores in the varenicline group relative to the placebo group, and N of 15 or 29 per group would have an 80% to detect differences. A sample size of 60 for both groups combined is at or above these estimates of group size needed from the above hypothetical analyses. Using specific cognitive tests (CPT or visual spatial dot measures) measures from previous experiments we conducted with Nicotine active and placebo spray in one study, and olanzapine vs haloperidol in another study, N Query Advisor 3.0 calculated group sizes needed for 80% confidence at 15-20 per group. Therefore, both these analyses suggest that a group size of 60 (30 per active and 30 per placebo group) is sufficient for our experimental design.

***Amendments to IRB Protocol***:

Summary of Amendments

*Amendment 1*: Modification of risk statements in consent form in response to discussion with FDA

*Amendment 2:* Addition of MATRICS Battery of neuropsychological test-

*Amendment 3*: Additional survey questions and proposed advertising flyer

Amendment 4: Minor changes in procedures; coordination with Stanley Grant; addition of inpatients.

*Amendment 5*: Addition of family history data and smell test (This part of protocol was not carried out extensively because of lack of funding for smell test battery).

*Amendment 6*: Approval of Israeli Collaborative Site.

*Amendment 7:* Approval of NKI collaborative site.

*Amendment 8*: Addition of Baseline/screening EKG test at start of study, minor changes in cardiac

Exclusion criteria and expansion to involve RPC inpatient subjects on CREF.

Amendment 9-*Spatial Memory Task In 'Controls*

The object of this amendment is to compare performance on the *Virtual Morris Water Maze Task*, a measure of spatial memory, memory task, that we have obtained dint he original main protocol, to normal controls, who will be the subject of this amendment.

Subjects:

The subjects for this sub study will be male and female controls, 21-65 years of age who do not have a diagnosis of schizophrenia or psychotic disorders, major depressive disorder, bipolar disorder, ADHD, autism spectrum disorder downs syndrome, or dementia or Alzheimer's disease. They will not be currently taking antipsychotic, antidepressant, amphetamines or ADHD medication or varenicline. They will not have a major neurological illness for which they are currently being treated with medication or electrical or prior surgical therapy. 15 subjects will be cigarette smokers and 15 subjects will be current non-smokers. Assuming a 10-15% drop out rate, to obtain 30 valid subjects we may enroll or consent up total of 35 subjects.

Subjects Recruitment:

Subjects will be recruited from NKI research outpatient clinic control pool and volunteers, students and staff members of Nathan Kline Institute and Rockland Psychiatric Center. If we do not find enough subjects from these sources and want to recruit from a larger pool from Rockland County through advertisements, we will submit an advertisement for approval to the NKI IRB.

Procedures:

1. The patient will have brief interview and fill out questionnaires to assessing his medical and psychiatric history, current treatments, medications, and cigarette smoking.

2. They will bee administered the RBANS neuropsychological battery. This is a paper and pencil short neurocognitive battery which takes about 20-30 minutes.

3. Take a computerized test, *Virtual Morris Water Maze Task,* in which they will move a pointer around a pool of water on the computer screen. This will take about a half hour or less.

(In Phase I patients had 4 hidden platform trial blocks of 3 trials each, with random placement of the platform in the four quadrants, and 60 seconds to locate the platform until the platform becomes visible by raising it above the surface of the water. Measures in Phase 1 were latency to finding the platform (seconds) and distance (path length/pool diameter). In Phase II there was one 45-second trial with the platform visible, and then a similar trial with the platform in the same location but removed from the visual environment).

No drug is administered in this study.

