***2.2 Patients***

***Number of Patients***. Up to 100 patients will be enrolled in the study and we expect a 10-20% drop out rate. Valid cases for analysis of each variable will be considered subjects who have completed at least 1 post-baseline evaluation on that variable.

***Inclusion Criteria***: Patients will be male or female, 18-65 years of age, with a DSM-IV diagnosis of schizophrenia or schizoaffective disorder determined by best estimate diagnostic approach using research DSM-IV criteria diagnostic checklist, review of chart history and data from structured interviews. Patients will be currently treated with antipsychotic medications, and be judged to have a clinically stable symptom picture and not currently in actue exacerbation of their psychotic symptoms. Patients will have a minimal level of cognitive impairment; defined by a total score of ≤90 on the Repeatable Battery for the Assessment of Neuropsychological Status [RBANS] (The total score for normal subjects is mean±sd 100±15). All schizophrenic patients will either be current cigarette smokers or patients who were regular cigarette smokers in the past, and are not currently smoking daily because they are hospitalized in a non-smoking facility.

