***Exclusion criteria***: Subjects will be excluded if they have a total PANSS score>80, have a PANSS depression item score >5, have a Calgary Depression score >20, have expressed definite suicidal ideation in the last month, or have made a documented suicide attempt or clinically serious documented suicide gesture in the last year. Subjects who have a history of multiple serious suicide attempts or clinically serious gestures in the past will be excluded. Subjects who meet DSM-IV criteria for current cocaine-crack, PCP, or methamphetamine abuse in the last month will be excluded. Patients who are currently smoking marijuana will be excluded. Patients with a current neurological CNS disorder such as seizure disorder or stroke in the last year, who are currently receiving medications specifically for these conditions, will be excluded. Patients with history of possible Downs syndrome, severe mental retardation, or dementia will be excluded. Subjects who have significant renal impairment (creatinine ≥ 1.5) will be excluded. Patients with acute exacerbations of their psychosis in the last month which are judged to be clinically significant, and have not re-stabilized, will be excluded. Patients with a documented history of a myocardial infarct, documented history of atrial arrhythmias or fibrillation within the last year, or a documented medical history of thromboembolic events will be excluded. Subjects who are currently treated with varenicline, at time of screening for the study, will not be enrolled in the study.

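### Amendment 9 controls are not subject to the marijuana and drug-abuse exclusions applied to patients, so the water maze difference may be understated

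*Protocol*

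**What the plan says.** Two sets of eligibility rules bear on this comparison.

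**Patients (Protocol, section 2.2, Exclusion criteria).** Two substance rules apply. The first is "Patients who are currently smoking marijuana will be excluded". The second is "Subjects who meet DSM-IV criteria for current cocaine-crack, PCP, or methamphetamine abuse in the last month will be excluded".

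**Controls (Protocol, Amendments to IRB Protocol, Amendment 9, Subjects).** The amendment sets out to compare patients' maze performance "to normal controls, who will be the subject of this amendment". Controls are "male and female controls, 21-65 years of age who do not have a diagnosis of schizophrenia or psychotic disorders, major depressive disorder", and the list continues with other psychiatric and developmental diagnoses and dementia. A major neurological illness under current treatment also excludes. On drugs the text says only: "They will not be currently taking antipsychotic, antidepressant, amphetamines or ADHD medication or varenicline". Of the 30 valid controls sought, 15 are to be cigarette smokers and 15 non-smokers; up to 35 may be enrolled.

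**What is recorded about controls (Amendment 9, Procedures, step 1).** Controls have a brief interview and "fill out questionnaires to assessing his medical and psychiatric history, current treatments, medications, and cigarette smoking". Marijuana and other drug use are not among the topics named.

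**The concern.** Amendment 9 exists only to contrast patients with normal controls on a spatial memory task. Nobody is randomised to be a patient or a control, so the comparison depends on both groups being selected by similar rules on anything that may affect memory. The protocol itself treats current marijuana smoking and recent abuse of three named drugs as reasons to keep people out of a study of cognition, yet it applies those rules to one side only.

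If some controls are current users and perform worse for that reason, the control mean falls and the patient deficit looks smaller than it is. Because the interview does not name drug use, the plan also gives no assurance that the data for a sensitivity analysis would exist.

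**Working it through.** **1. The criteria side by side.**

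| Criterion | Patients (2.2) | Controls (Amendment 9) |
|---|---|---|
| Current marijuana smoking | excluded | not named |
| Cocaine-crack abuse, past month | excluded | not named |
| PCP abuse, past month | excluded | not named |
| Methamphetamine abuse, past month | excluded | partly covered: current amphetamines, listed beside ADHD medication |
| Substance-use diagnosis in general | not named | not named |
| Toxicology test | none described | none described |

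A current marijuana smoker who meets all other criteria is thus barred as a patient and admitted as a control. The mismatch follows from the text alone.

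**2. The amendment's own figure.** The enrolment ceiling of 35 is meant to yield 30 valid controls after 10-15% dropout. 30/(1 − 0.10) = 33.3, so 34; 30/(1 − 0.125) = 34.3, so 35; 30/(1 − 0.15) = 35.3, so 36. The stated 35 is reasonable and not in dispute.

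**3. Size of the shift.** Let p be the share of controls who are users, d their deficit in SD units, and D the true patient-control difference. The control mean falls by p × d, and the observed difference is D − p × d. None of p, d or D is in the documents; all values below are assumptions.

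- Low end: p = 0.10 (3 of 30), d = 0.3, shift = 0.03 SD.
- High end: p = 0.30 (9 of 30), d = 0.6, shift = 0.18 SD.
- p = 0: shift = 0.

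As a share of D:

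- D = 0.5 SD: 0.03/0.5 = 6% to 0.18/0.5 = 36%.
- D = 1.0 SD: 3% to 18%.

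**4. Effect on power, for illustration.** Take 30 controls and 60 patients, two-sided 5% level. The 60 is the planned trial size in section 3.2. Section 2.6 C adds the maze at U.S. sites only, so the number of patients with maze data is not given. A narrower assumed range is used here: p = 10-20%, d = 0.3-0.5.

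| True D | Observed D | Power without users | Power with users |
|---|---|---|---|
| 0.5 SD | 0.47 to 0.40 | 61% | 56% to 43% |
| 0.8 SD | 0.77 to 0.70 | 95% | 93% to 88% |

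**5. The shift against sampling error.** With the same group sizes the standard error of the difference is √(1/30 + 1/60) = 0.22 SD. Even the assumed upper shift of 0.18 SD is below one standard error.

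**The case against.** The case against has several parts, and much of it stands.

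- **Patients are not shown to be drug-free.** A reader might infer that patients are screened clean while controls are not. The text does not support this. Use of the three named drugs short of DSM-IV abuse is allowed, and no drug test is described. The contrast between groups is narrower than use against no use.
- **Controls are not wholly uncovered.** Amphetamines are named. The wording reads as medication, but it reaches one stimulant class at least in part.
- **Users might still come to light.** A reader might infer that users among the controls could never be identified. The protocol only summarises the interview topics, and substance problems could emerge under psychiatric history. What can be said is that drug use is not named, so its capture is not assured.
- **The percentages are assumptions.** A reader might take 6-36% as an estimate. It is not. The 0.5 SD denominator may also be small: section 2.2 requires an RBANS total of 90 or less against a norm of 100 ± 15, so every eligible patient is at least (100 − 90)/15 = 0.67 SD below the norm on that battery. RBANS is not the maze, but a larger deficit is plausible, and the relative loss would then be smaller.
- **The direction is benign.** Worse-performing controls pull the result toward no difference and would not create a false patient deficit.
- **Age is a separate, minor matter.** For patients the protocol says "Patients will be male or female, 18-65 years of age", while controls start at 21. A reader might tie this to drug-related masking, but the two are unrelated. If ages were uniform, the mean would move only from 41.5 to 43.0 years, and an SAP may already specify age adjustment.

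None of this removes the mismatch itself. Eligibility is settled in the protocol, and Amendment 9 is the working text for the control group, with its own subjects, recruitment and procedures.

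**Conclusion.** The point holds in a narrow form. Amendment 9 does not carry over the marijuana and drug-abuse exclusions of section 2.2, so a person ineligible as a patient on those grounds can be counted as a normal control. If such people are enrolled and perform worse, the maze difference is understated by p × d. That is 0.03-0.18 SD under the assumptions shown and nil if no control is a user; the documents allow no firmer figure.

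The consequence is confined to this add-on comparison. The randomised varenicline-placebo comparison, the MATRICS primary outcome and the main sample size are untouched. This is an inexpensive improvement, not a serious defect.

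**What to change.** In Amendment 9, Subjects, add one sentence applying to controls the section 2.2 exclusions for current marijuana smoking and for DSM-IV abuse of cocaine-crack, PCP or methamphetamine in the past month. In Procedures, step 1, add drug use to the topics recorded, so that any remaining difference can be described and examined in a sensitivity analysis.

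The change belongs on the control side, because the amendment describes the patients' maze data as already obtained and the controls as still to be recruited. The cost is one sentence and one interview question for at most 35 people, with slightly slower recruitment of controls.
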